**Project summary**

This is a randomized, single-blinded, parallel-controlled, three-group trial. A total of 66 females (mean age 19 years) with poor body posture were recruited from a local university and randomly divided into three groups, Pilates combined with breathing exercise training (PRT) group, Pilates group (PLT), and control group (CON). Randomized participants in each intervention arm will receive a three weekly, 60-minute exercise program for 16 consecutive weeks. Primary and secondary outcome measures will be collected at baseline, 8 weeks, and 16 weeks. An innovative inference reached that PRT can stimulate the diaphragm and strengthen the deep stabilizing muscles and trunk control, the function of the respiratory system may be improved to a certain extent by exercising the core muscles, including the respiratory muscles. It also indirectly affects muscle balance, resulting in improved static postural stability. Thus, the potential mechanism of linkage mechanism shall exsit between respiratory muscles and postural control during Pilates practice that warrants further study. Based on theoretical considerations and previous research on PRT, the overarching working hypothesis is that PRT will show better performance results on primary outcome measures compared to both the PLT training and CON.

**Rationale & background information**

Regular exercise behavior is positively related to the health of respiratory function and the development of postural muscle groups^1^. Exercise or sole respiratory muscle training have been demonstrated to be effective in improving dyspnea in patients with the chronic obstructive pulmonary disease^2^. Pilates is an integrated exercise focusing on strength, core stability, flexibility, muscle control, posture, and breathing^3,4^. During exercising Pilates, it allows one to exercise the deep muscle groups that maintain and coordinate body posture while supporting and protecting the spine^6,7,11^. The deep and core muscles, which include the transverse abdominis, multifidus, pelvic floor and diaphragm muscles, can be activated to provide alignment and support for posture^12,13,14^. In addition, these deep and core muscle groups can strengthen small muscles in the abdomen, lower back, hip and spine, which would further balance back and abdominal muscle strength and correct poor body posture^5^. However, a problem exist in the related studies is that few studies have been conducted to examine the effectiveness of exercise can effectively improve abnormal body posture while intervening to improve respiratory function or whether exercise improves respiratory function by targeting abnormal body posture muscle groups. Therefore, this study aimed to examine the effects of exercise on lung function, body posture and postural stability among female college students with poor body posture and the linking effects of an exercise intervention on respiratory and postural stabilizing muscle groups.

**Study goals and objectives**

The primary aim is to investigate whether the PRT program can improve primary outcome measures of lung function and secondary outcome measures of standing posture and static postural stability in female university students. Two secondary aims are to be examined: (a) whether there is a synergistic effect exist in the improvements of lung function and body posture and (b) whether respiratory muscles can mediate synergistic changes in lung function and posture.

**Study design**

We propose to conduct a 4-month randomized, controlled, single-blind trial with three arms. The study will be recruited through posters and presentations on healthy lifestyle promotion, where eligible participants will undergo initial screening, consent and baseline assessments, and will be numbered and randomized into three equal groups. Details regarding study population, subject recruitment, randomization, intervention components, and outcome assessments are described below.

**Study Population**

The intervention will be directed toward individuals who have a poor body posture, with the following eligibility criteria.

Inclusion criteria will include (a) long-term sedentary study work; (b) no regular daily exercise habit; (c) had one of the poor body postures such as rounded shoulders (natural upright posture with strongly forward-rotated upper limbs and raised shoulder blades), forward head posture (forward angle <48°), anterior pelvic tilt (anterior pelvic tilt angle >15°). Participants were excluded if they displayed any physical unfitness for exercise or time conflict with intervention.

**Recruitment Sources and Procedures**

Potential study participants will be recruited through three major sources: (1) recruitment information posted on WeChat (online) circle of friends; (2) poster campaign; (3) lectures about healthy lifestyle promotion. The study participants will be

recruited from the University in Nanjing. To reduce potential expectation bias, participants will be informed that this study will compare three different groups and that participants will be randomly assigned to either group.

Postural assessments will be conducted by researchers with a professional background in sports human science.

**Baseline Assessments**  Those individuals who are eligible after screening will then be given informed consent materials followed by a baseline evaluation conducted by a study assessor. The baseline assessments will include body mass index (BMI), height, bust circumference, waist circumference, hip circumference, and collection of demographics, health status, and medication use. This will be followed by assessments of lung function, and static posture stability. At that time, the intervention activities involved with the study will be reiterated to the eligible individuals. Those who meet all study criteria, are clear about research procedures, have completed baseline assessments, and give final consent will then be randomized.

**Randomization and Blinding**

Eligible participants who have signed the informed consent form will be entered into the computer and divided into three equal groups.

All study assessors who will collect study outcome measures will be blinded to study hypotheses and group allocation. Blinding will be strictly maintained by emphasizing to assessors the importance of minimizing assessment bias and regular checking of the blinding status. Participants will be instructed not to reveal their group status to the study assessors at any time.

**Intervention Instructors**

The PRT was conducted at 16:00-18:00 on Monday, Wednesday and Friday, whereas PLT was conducted at the same time slots on Tuesday, Thursday and Saturday. One qualified Pilate instructor trained the two groups in the same gym hall to ensure that the participants in the two exercise groups received the same training guidance.

**Class Location**

The first eight weeks involved supervised exercise at a gym, followed by eight weeks (weeks 9-16) of home-based online training.

**Intervention Adherence**  Every participant is expected to commit to a four-month period of intervention. Attendees will be motivated to join every session of the intervention (totaling 48), anticipating a compliance rate exceeding 85%. A research assistant will meticulously track class participation every two weeks in the initial month, followed by monthly checks thereafter. Individuals will be classified as drop-outs if they discontinue participation in the intervention, do not come back for assessments, or are absent for over four weeks in a row during their designated intervention. Every participant ceasing participation in the intervention sessions will be promptly reached out to and urged to come back for all assessments. Every participant who dropped out will be subjected to an exit interview to ascertain their reasons for discontinuing the study.

**Drop-outs**

Unavoidable drop-outs, such as scheduling conflict, are anticipated. Based on our prior studies involving Pilates, we estimate a 15% dropout rate for the overall study. The proposed sample size will take into account this anticipated dropout rate.

**Outcome Measure**

All primary and secondary measures will be ascertained at baseline, 8 weeks (midpoint), 16 weeks (intervention termination).

**Study Assessors**

All study assessors will be oriented and trained to follow the general assessment

guidelines and protocols established by the research project. Training will be conducted by the Principal Investigator. Following the established assessment protocol, the assessors will also be trained by a board-certified neurologist to use the Unified Parkinson’s Disease Rating Scale. Inter-rater reliability among assessors will be established via an intraclass correlation method.

**Methodology**

**Outcome measures**

The Lung Function Tester (AS-507, Japan) was employed to evaluate respiratory capacity, following a comprehensive lung function analysis that encompassed forced vital capacity (FVC), forced expiratory volume in the first second (FEV1), FEV1/FVC, peak expiratory flow rate (PEFR), maximum ventilation volume (MV), minute ventilation volume (MV), and tidal volume (TV). The test for respiratory function was performed thrice, with the highest score being documented. Respiratory muscle function was measured using PEFR and MVV, while lung function was assessed using FVC, FEV1%, MV, and TV. The subjects were advised to remain seated for a duration of 10 minutes prior to the examination to prevent any possible respiratory impacts.

Photogrammetry^10^ was employed to evaluate the stationary standing stance. The participants were instructed to maintain a fully relaxed and natural posture, oriented towards a hypothetical point on the wall across. Red patches were used to mark the seventh cervical spinous process, the tip of the shoulder, and the ear screen. Concurrently, the front upper and back upper parts of the iliac spine were identified by a yellow patch. The subjects positioned their left shoulder against the wall, facing the chart for assessing posture. Positioned two meters away from the body assessment chart, the photo tripod holding the digital camera aligned perfectly with the participant's right shoulder. The smaller the data, the better the static postural stability. Side images were captured, and the participant's round shoulder angle (RSA) and anterior pelvic tilt angle (APA) while standing were computed using Photoshop. Manual measurement of the gap between the two shoulder peaks (DSP) and the anterior pelvic tilt dimension (APD) was performed using a soft ruler tape. Positioned parallel to the body's frontal axis, the soft tape gauges the peak points between the left and right shoulders. Additionally, the front part of the pelvic tilt was gauged 2 cm beneath the participant's navel.

Participant characteristics. Demographic and health characteristics of participants will be collected at baseline to describe the sample, compare conditions, and investigate characteristics associated with outcomes. These measures will include age, gender, use of medication, resting blood pressure, body weight (kg), and body height (cm), Bust Circumference (cm), Waist Circumference (cm), Hip circumference (cm). Blood pressure will be measured with the use of an automated device (Omron HealthCare). Body weight and height will be assessed through the use of digital scales (Health o Meter@).

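### Recording the highest of three trials suits maximal efforts but not tidal volume or minute ventilation; it costs some precision there and leaves the derivation of FEV1/FVC open

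*Protocol*

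**What the plan says.** The protocol's Outcome measures section lists seven respiratory parameters: FVC, FEV1, FEV1/FVC, PEFR, maximum ventilation, minute ventilation and TV. The last three appear as "maximum ventilation volume (MV), minute ventilation volume (MV), and tidal volume (TV", so the abbreviation MV stands for two different quantities. The next sentence gives the recording rule: "The test for respiratory function was performed thrice, with the highest score being documented". No parameter is excepted, and nothing says how FEV1/FVC is formed from the three trials.

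The section then divides the battery. PEFR and MVV represent respiratory muscle function, "while lung function was assessed using FVC, FEV1%, MV, and TV". Study goals and objectives names "primary outcome measures of lung function and secondary outcome measures of standing posture and static postural stability". TV and MV are therefore primary measures. MV is most naturally minute ventilation here, because maximum ventilation is placed with muscle function as MVV. The ratio is primary only if FEV1%, which is not defined, means FEV1/FVC.

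On test conditions: "The subjects were advised to remain seated for a duration of 10 minutes prior to the examination". Quiet breathing for TV and minute ventilation is implied by the nature of the measures and by this rest. It is not stated.

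**The concern.** In a maximal effort, most errors fall short of the person's capacity, so the best of three attempts is a sensible estimate. TV and minute ventilation have no ceiling of that kind. Their trial-to-trial errors go both ways, and the highest of three simply picks the largest upward deviation. Three trials are performed, but the rule keeps less information from them than an average would.

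The ratio raises a separate question. A short FVC raises FEV1/FVC, so a highest-of-three rule applied to the ratio itself would tend to favour the less complete blow.

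At stake is the precision of primary measures in a trial of 66 women in three equal groups. The rule also governs data capture: if only the highest value is written down, no later analysis plan can recover the other two.

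**Working it through.** The protocol gives no reliability, error SD or power figure for these measures, so there is none to reproduce. Its inputs are three trials, the maximum recorded, and 66 / 3 = 22 per group (66 × 0.85 / 3 = 18.7 after the expected 15% dropout). Everything else is an assumption.

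**TV and minute ventilation.** Take three independent normal trials with within-person SD *s*.

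- Expected shift of the maximum: 3 / (2√π) × *s* = 0.846*s*.
- Variance of the maximum: (1 + √3/(2π) − 9/(4π)) × *s*² = 0.559*s*².
- Variance of the mean of three: *s*²/3 = 0.333*s*².
- Ratio: 0.559 / 0.333 = 1.68, that is 68% more error variance. Simulation agrees.

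Next, set the total variance of a single trial to 1 and let *w* be the within-person share. The outcome variance is (1 − *w*) + *w*/3 for the mean and (1 − *w*) + 0.559*w* for the maximum. The loss of effective sample is 1 minus the inverse of their ratio.

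| Assumed *w* | Mean of three | Maximum | Ratio | Effective sample lost |
|---|---|---|---|---|
| 10% | 0.933 | 0.956 | 1.024 | 2.4% |
| 20% | 0.867 | 0.912 | 1.052 | 5.0% |
| 30% | 0.800 | 0.868 | 1.085 | 7.8% |
| 50% | 0.667 | 0.780 | 1.170 | 14.5% |

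With 22 per group this is between 22 × 0.024 = 0.5 and 22 × 0.145 = 3.2 participants per group. For an assumed difference of 0.9 true-score SD between two groups of 22 (two-sided 5%, normal approximation), power with the mean against the maximum is 83.4% vs 82.5% at *w* = 10%, 81.8% vs 79.8% at 20%, 79.7% vs 76.5% at 30%, and 73.4% vs 66.7% at 50%. These figures are for an unadjusted comparison at one visit. Where baseline adjustment removes stable between-person variance, error is a larger share of what remains.

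**Can the shift reach the group difference?** Only if trial-to-trial variability comes to differ by arm. If the coefficient of variation (CV) in one arm fell by 25% from 10 to 20%, the artefact would be 0.846 × CV × 0.25, that is 2.1 to 4.2% of the mean. Nothing in the protocol shows that this happens.

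**FEV1/FVC.** Simulation with assumed FEV1 2.75 L and FVC 3.2 L (ratio 0.859), half-normal shortfalls drawn independently, FEV1 shortfall SD 2%, and FVC shortfall SD 2% or 4%:

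| FVC shortfall SD | Highest ratio | Highest FEV1 / highest FVC | Ratio from test with largest FEV1 + FVC |
|---|---|---|---|
| 2% | 0.872 | 0.859 | 0.859 |
| 4% | 0.896 | 0.865 | 0.863 |

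The highest ratio exceeds highest FEV1 / highest FVC by 1.3 and 3.0 points (from unrounded values). Its error SD is 0.0118 against 0.0070 (1.7 times) and 0.0232 against 0.0113 (2.1 times). It comes from the blow with the smallest FVC in 69% and 81% of cases. With shortfalls correlated at 0.8 within a blow, the excess drops to about 0.8 to 2.4 points.

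**The case against.** The strongest reply is that the rule is the same in every arm and at every visit, the assessors are blinded to allocation, and the analysis is ANCOVA on baseline. A common upward shift then largely cancels. That stands. A reader might infer that the rule biases the treatment comparison, for example because unblinded participants try harder in one arm. The protocol gives no evidence of differential effort or of changing variability, so this remains a possibility and not a finding.

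Second, the sentence can be read in more than one way. It refers to the test and its score in the singular, so it may mean the values of the best overall test, or the highest volumes with the ratio derived from them. On those readings the ratio needs almost no correction, as the second table shows. A reader might also infer that poor effort always scores best. It does not: the highest ratio comes from the least complete blow often but not always, and a generally weak blow lowers FEV1 as well. Nor is the ratio established as a primary measure while FEV1% is undefined.

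Third, the loss is small if trials are repeatable, and against a single trial the maximum is the less noisy choice (0.559 against 1.00 *s*²). Both are true. The comparison that matters is with the mean of three trials that are performed anyway.

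Finally, Study Assessors and Testing Procedures refer to assessment protocols that may hold finer recording rules. If so, the main text should agree with them.

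**Conclusion.** The point holds for TV and minute ventilation. As written, the rule records a maximum for two non-maximal primary measures, which raises their level by about 0.85 within-person SD and carries 68% more error variance than averaging. These two figures assume independent, normally distributed trial errors. The main cost is precision: about 2 to 5% of the effective sample if within-person error is 10 to 20% of total variance, and about 8 to 14.5% if it is 30 to 50%. Those shares are assumptions. The documents do not support going further to claim a biased group difference.

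For FEV1/FVC the fault is lack of specification. An overstatement of roughly 1 to 3 points arises only if the highest ratio itself is recorded, and its size depends on assumed volumes and shortfalls. If values come from the best overall test, it is nearly absent.

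**What to change.** Replace the single rule in Outcome measures with one by type of measure:

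- FVC, FEV1, PEFR and maximum ventilation: keep the highest of the three trials.
- TV and minute ventilation: use the mean of the three trials.
- FEV1/FVC: highest FEV1 divided by highest FVC.
- Store all three trials for every parameter.

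In the same edit, give maximum and minute ventilation separate abbreviations and define FEV1%, so that the primary measures affected are clear.

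No additional testing is needed. The one real cost concerns tests already made: the individual trials must be retrievable from the device or source records. The same rule must apply at baseline, week 8 and week 16, because mixing maxima and means across visits would put the shift into the change scores.

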**Testing Procedures**

The assessment protocol will be standardized to ensure measurement consistency between assessors and across different sites and to minimize effects of motor fluctuations. Efforts will be made to schedule all assessments at the same time of day and to perform them in the same.

**Safety considerations**

Adverse events, major or minor, during a class session or outside classes (school, lab testing) will be documented in a project adverse log and, in the event of observing a major adverse event, reported immediately to the Ethics Committee of Nanjing Normal University.

In-class exercise safety will be closely monitored during the entire length of the trial by research staff and class instructors. Staff will make periodic visits to classes to check safety status and address concerns related to the exercise programs. Intervention instructors will be asked to monitor participants for symptoms of any discomfort. Modifications in the training protocol will be made, upon approval of the research staff, on an individual basis as necessary.

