**Duration of the project**

**Interventions.** The protocol will ensure that each exercise group has a consistent intervention schedule on key training parameters involving duration (60 minutes per session), frequency (3 times per week), and training structure (i,e., a 5-minute warm-up, Pilates training, a 10-minute breathing trainer training PRT group only, and a 5-minute cool-down). Participants in all two conditions will be instructed not to engage in any additional home practice.

**Pilates.** The protocol consists of 24 Pilates movements^8^. The names of 24 movements are as follows: drawing circles with hands, march stepping, four-legged swimming, curl-ups, 100 taps, plank, chest lift, single-leg drawing circles, quadriceps stretch, opposite arm and leg reach, supine spinal rotation, prone props, prone swimming, swan, v-spins, con-con dance, double leg extensions, mermaid side bends, side lying pedal cycle, shoulder bridge, prone swimming, quadriceps stretch, kneeling side kick, neck and shoulder stretch.

The 16-week exercise program was divided into four stages (ice breaker, for beginners, for intermediate, and for advanced), and the quality of movements and exercise intensity were gradually increased along with training process. Because the goal of the protocol is to train participants' in core muscles and correct poor posture, the protocol is specifically designed to challenge core muscle control and spinal flexibility and functional training modalities. Instruction will cover learning new forms and reviewing and practicing forms learned in previous sessions.

At the end of each phase, self-perceived exercise intensity was assessed using the Chinese version of the Rating of Perceived Exertion (RPE) scale^9^. Exercise intensities were ranged from light (RPE 11) to lightly hard (RPE 13). The exercise load was arranged 3-4 sets per group and 6-9 repetitions per set. Exercise intensity as measured by heart rate were recorded before, during and after each training session.

**Breathing exercise.** In the PRT group, participants were required to use a breathing trainer (TRI-BALL breath-trainer) to perform respiratory muscle exercises (10 minutes) immediately after the Pilates training. Participants were instructed to perform fast and forceful inspirations to achieve maximal inhalation and exhalation during every breath.

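### Safety monitoring is described only for classes, yet half the sessions are home-based online and the control group has no classes, so adverse-event capture is likely to be uneven

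*Protocol*

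**What the plan says.** The Protocol's Safety considerations section sets out how events are recorded and how participants are watched.

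- **Recording:** "Adverse events, major or minor, during a class session or outside classes (school, lab testing) will be documented in a project adverse log". A major event, once observed, goes at once to the ethics committee.
- **Watching:** "In-class exercise safety will be closely monitored during the entire length of the trial by research staff and class instructors". The means given are that instructors look out for discomfort and that "Staff will make periodic visits to classes to check safety status and address concerns related to the exercise programs".

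The Class Location section gives the setting: "The first eight weeks involved supervised exercise at a gym, followed by eight weeks (weeks 9-16) of home-based online training". Under Intervention Adherence, the same section puts the total at 48 sessions.

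The Duration of the project section divides the 16 weeks into four stages (ice breaker, beginner, intermediate, advanced) and says that "the quality of movements and exercise intensity were gradually increased along with training process". It gives no stage lengths.

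Sessions are described for the two exercise arms, Pilates plus breathing training (PRT) and Pilates alone (PLT). None are described for CON.

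**The concern.** The safety text is built around a class that staff can visit and an instructor can observe. That fits the gym phase. It does not say what happens once training moves into participants' homes, and it offers nothing comparable for CON. The Problems anticipated section still treats online delivery as a contingency for a coronavirus outbreak, although Class Location makes it the plan for half the trial. This suggests that the safety text was not adapted to the delivery plan.

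What is at stake is how the safety data can be read. If events are actively looked for in one setting and not in another, a lower count in weeks 9-16 or in CON may reflect less looking rather than less risk. Because intensity rises through the programme, the later and harder training falls in the phase with the least described observation. In PRT, the breathing-trainer component also loses its described observation in that phase.

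**Working it through.** **Inputs.** Three sessions a week for 16 weeks (Project summary); 48 sessions in total, with weeks 1-8 in the gym and weeks 9-16 at home online (Class Location); four stages of unstated length (Duration of the project).

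**Step 1: the plan's own total.** 3 × 16 = 48, which reproduces the stated figure.

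**Step 2: share outside the described setting.** Home sessions = 3 × 8 = 24, and 24 / 48 = 50% for each exercise participant. CON has no described sessions, so in-class monitoring covers none of its 16 weeks.

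**Step 3: which stages fall at home.** This needs an assumption about stage lengths.

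| Assumed stage lengths (weeks) | Intermediate stage starts | Weeks of intermediate and advanced stages in the gym |
|---|---|---|
| 4/4/4/4 | week 9 | 0 of 8 |
| 2/6/4/4 | week 9 | 0 of 8 |
| 2/5/5/4 | week 8 | 1 of 9 |
| 2/4/5/5 | week 7 | 2 of 10 |
| 1/5/5/5 | week 7 | 2 of 10 |

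With equal stages, both upper stages fall wholly in the home phase. With the unequal splits shown, most of their weeks still do (8 of 9, or 8 of 10).

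**Step 4: does any other described contact fill the gap?**

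- *Heart rate around each session and perceived exertion at the end of each stage (Duration of the project).* These may extend to home sessions, but they measure exercise intensity and do not ask about events. They do not apply to CON.
- *Attendance checks (Class Location, Quality assurance).* These count participation and ask nothing about symptoms.
- *Prompt contact with those who stop attending, and exit interviews (Class Location).* These may bring an event to light, but only among people who leave.
- *Assessments at weeks 8 and 16 (Outcome Measure).* These are planned for the trial's outcomes in all arms, but no adverse-event inquiry is listed.
- *Follow-up call on physical status (Follow-up).* This comes after the intervention has ended.

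None of these is a described adverse-event inquiry during weeks 9-16, and none provides CON with a counterpart to in-class observation.

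**Step 5: which arms differ.** PRT and PLT share one instructor and one gym hall (Intervention Instructors) and the same change of setting after week 8. The text gives no ground for unequal capture between them. The contrast is between the exercise arms and CON. It exists from week 1, when the exercise arms are observed in the gym and CON is not.

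**The case against.** The strongest reply is that the two sections need not conflict. The log covers events "during a class session or outside classes (school, lab testing"), and the bracket can be read as giving examples, so home is not excluded. The home training is online. If it is live, an instructor can see participants and staff can join, and the stated monitoring could carry on in another form. Intensity is also modest, with perceived exertion between 11 and 13. Adverse events are not a listed outcome, no comparison of them is planned, and details of safety reporting may sit in a statistical analysis plan that is not shown.

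Much of this stands, and it rules out several stronger readings that a reader might infer:

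- *That adverse-event capture fails in weeks 9-16.* The log's scope does not support this. What is missing is a described way of eliciting events.
- *That home sessions cannot be observed at all.* The Protocol does not say whether they are live or recorded.
- *That the two most demanding stages are certainly at home.* This depends on stage lengths that are not given.
- *That PRT and PLT are monitored differently, or that the home phase creates the difference between arms.* Neither follows from the text.

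The reply does not remove the central point. A log records what reaches it, and the only active route described is observation in class. How events are found is a matter of conduct that this Protocol itself sets out, and what it sets out does not say how it applies to half the sessions or to CON. Even a plain listing of events by arm would be affected by unequal looking, whether or not a formal comparison is planned.

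**Conclusion.** The point holds in a limited form. In-class monitoring is stated for the whole trial, but 24 of 48 sessions (50%) are home-based online, and the Protocol does not say how monitoring applies to them. CON has no described classes in any of the 16 weeks. With no active elicitation described for home sessions or for CON, capture is likely to be less complete in weeks 9-16 and unequal between the exercise arms and CON throughout.

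The 50% figure rests only on the stated schedule. The loss in weeks 9-16 would be smaller if the online sessions are live and instructor-led. Placing the intermediate and advanced stages wholly in the home phase assumes stages of equal length. The number of events missed cannot be estimated, because the Protocol gives no expected event rate. The primary efficacy analysis is not affected. The change is nonetheless worth making, because safety counts collected as described could not be read reliably across arms or phases.

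**What to change.** 1. Reconcile Safety considerations with Class Location: state whether the online sessions are live or recorded, and how the described monitoring applies to them. Which arrangement to adopt is for the sponsor and the investigator to decide.
2. Ask all three arms the same short adverse-event question, in the same words and on the same schedule. The minimum is the existing week 8 and week 16 assessments, which close the two phases.
3. Report events by arm and by phase (weeks 1-8 and weeks 9-16).

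**Cost.** At the minimum, this means revised wording and one added question at visits that already take place. More minor events will be recorded. Two inquiries eight weeks apart also rely on recall. Asking more often would reduce that, but any contact between these visits would be new for CON, which is one third of participants (66 / 3 = 22 with three equal groups).
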